## **Overview**

There will be a secondary distribution of self-test kits demonstration project to facilitate early detection of positive cases and appropriate linkage to COVID-19 care (home or facility based).

COVID-19 positive patients (index cases) from the HCW, OPD and Outbreak investigation in congregate setting studies will be screened for eligibility and asked for informed consent to participate. The national guidance is that all close contacts of an index case should be deemed positive and treated as such (32). However, the decision to abandon contact tracing in Malawi was largely taken due to the labour and resource-intensive nature of professional Ag-RDTs or PCR for contacts.

This study's approach is to offer COVID-19 self-test kits to the contacts and collect data via the index case, which is relatively inexpensive. Making a generalized assumption that all contacts should be deemed positive may inadvertently put individuals at the front of stigma and economic exclusion.

There are very limited data on COVID-19 secondary distribution in low-and-middle-income-countries and this is a good opportunity to test the model which may as well become the mainstay to manage large testing volumes in times of great demand during COVID-19 waves.

Participants will be provided with brief training on how to demonstrate correct use of nasal swabbing and testing and information leaflets including direction on how to access web-based or WhatsApp video clips.

## **Activities**

### **Epidemiological**

A structured questionnaire (CC01) shall be used to interview index cases who tested positive for COVID-19 from any of the use cases at time of testing positive. The questionnaire will collect information on social demographic indicators about the index, as well as COVID-19 symptoms, risk and testing, and information about their close contacts. The index will themselves fill in data on their contacts onto a contact log (CC03).

A second structured questionnaire (CC02) will be used to interview index cases 7-14 days after recruitment to follow up on the details of each of their listed contacts via telephone interview (the index will use their log to report this data back). Please note at no point do we call the contacts themselves.

### **Qualitative**

A subsample of 20 index patients will be selected to ascertain the acceptability of the use-case in line with Proctor's implementation outcomes (Client SSI).

Study coordinators and 2 study providers will be interviewed to write up the TIDieR description for this use-case, as well as to input into the acceptability of the use-case in line with Proctor's implementation outcomes (Provider SSI topic guide & CK01).

### **Cost and cost effectiveness**

A subsample of 20 participants will be selected to receive a structured questionnaire asking clients about their time spent testing, and any costs incurred in accessing COVID-19 testing (Patient cost questionnaire\_Final **Secondary**). This tool is different to Patient cost questionnaire\_Final tool used in the other use-cases, as it seeks to understand costs of delivering the test kits to contacts, instead of the costs of receiving a test. Written consent is taken in advance, and the interview is administered on day 14 during the follow up phone call.

### **Sample size**

The number of contacts will be determined by the number of index cases and is not known at the time of design. However, assuming 2% of all our screening tests from the above use cases are positive i.e., ~30,000 overall tests, then about 600 index cases will be generated. Assuming there would be three household contacts and 2 two close contacts, then a total of 3000 contacts will be approached. When oral antivirals become available in Malawi, information on treatment eligibility and how to access antivirals will be included.

For statistical power with the secondary distribution of self-test kits, we assume 60% of contacts will be willing to self-test for COVID-19 if offered. For the sample proportion to be estimated to within  $\pm 0.05$  (5%) using the 95% confidence level, a sample of 370 contacts accepting self-tests is required.

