|                                             |                                                          |                                                                                   | iii. Sub-sample participant cost interviews, and provider cost observations establishing cost of process                                                                                                                                                                      |                                                                                                                                                                                                                                                                                                                                                           |                  |
| 4. Secondary distribution of self-test kits | Self-testing:
Demonstration project evaluation | Proportion of contacts self-tested for COVID19 (contact uptake of self-test kits) | i. Epi interviews establishing participant sociodemographic profiles
ii. Sub-sample qualitative interviews establishing acceptability of demonstration model
iii. Sub-sample participant cost interviews establishing cost of model ( no provider observations ) | Any positive participant from the use-cases.
All eligibility assessed
i. All receive baseline epi interview, and telephone follow up after 14 days
ii. subsample of 20 qualitative interviews
iii. subsample of 20 patient-level costing interviews

Minimum requirement of 370 contacts to ascertain uptake i | 6,000 self-tests |

|  |  |  |  |  |
|--|--|--|--|--|
|  |  |  |  |  |
|  |  |  |  |  |
|  |  |  |  |  |
|  |  |  |  |  |
|  |  |  |  |  |
|  |  |  |  |  |
|  |  |  |  |  |
|  |  |  |  |  |

MLW: Malawi Liverpool Wellcome Trust Clinical Research Programme; PSI: Population Services International

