Outcomes will be collected by telephone interview with the index case two weeks after enrolment. The data from the phone interview will include if the index delivered the COVID-19 self-test kits to the contacts or not, contact used the test kits as advised and if they disclosed the results to index. No personal identifiers will be collected on the contacts, but we will ask the index to identify any known high-risk factors (age over 65 years, or over 50 years with co-morbidity) that would be a potential indication of eligibility for outpatient treatment of the tested contact. If consent has been taken, the participant cost survey will then be administered over the phone as well.

A person shall be considered a contact if they had any one of the following exposures to a confirmed case as suggested by WHO(33):

- face-to-face contact with a confirmed case within 1 meter and for at least 15 minutes;
- direct physical contact with a confirmed case;
- direct care for a patient with probable or confirmed COVID-19 disease without the use of recommended PPE.

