## 5.8. Overall sample size considerations

For the non-randomized controlled study: with an assumed harmonic mean number of 20 and 35 HCWs (common standard deviation: 12) in SOC and the PCI arm confirmed (either by PCR or by repeat professional Ag-RDT) COVID-19 diagnosed within three months, 6 clusters per arm of ~100 HCWs each, the study will have 84.1% power to detect the stated difference of harmonic count of 15.

For components offering self-testing, we conservatively assume that 60% of participants will be willing to self-test for COVID-19 if offered. For the sample proportion to be estimated to within +/- 0.05 (5%) using the 95% confidence level, a sample of 369 participants would be required. Whereas for components offering professional COVID-19 Ag-RDTs we conservatively assume that 70% of participants in each of the targeted groups will accept to be tested for COVID-19. For the sample proportion to be estimated to within +/- 0.05 (5%) using the 95% confidence level, a sample of 323 participants would be required.

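### The minimum of 370 contacts for ±5 points assumes independent contacts, although about five share one index case; the stated minimum is too low, but the expected 3000 would be ample.

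*Protocol*

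**What the plan says.** In Protocol section 5.1.4 (Sample size) the planning assumption is "we assume 60% of contacts will be willing to self-test for COVID-19 if offered". For ±5 points at 95% confidence it concludes that "a sample of 370 contacts accepting self-tests is required". Table 1 (section 5.1) presents the number as a floor: "Minimum requirement of 370 contacts to ascertain uptake". The executive summary also gives 370 for components offering self-testing, and section 5.8 gives nearly the same figure: "estimated to within +/- 0.05 (5%) using the 95% confidence level, a sample of 369 participants would be required".

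The same sample size text sets the expected scale. It starts from about 30,000 tests at 2% positivity: "then about 600 index cases will be generated". It continues "Assuming there would be three household contacts and 2 two close contacts", "then a total of 3000 contacts will be approached". It also says that the number of contacts is unknown at the design stage.

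Section 5.1.4 (Activities; Recruitment process) describes how contacts are reached and measured:
- The index case is given two kits for each named contact and passes them on.
- The telephone interview with the index case asks, among other things, "if the index delivered the COVID-19 self-test kits to the contacts or not".
- Contacts themselves are never telephoned.
- The results are stored as one aggregate record per index case.

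No design effect or intraclass correlation (ICC) is given for this component. The term ICC appears only in the list of acronyms.

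**The concern.** The precision formula behind 370 counts each contact as a separate piece of information. In this model the contacts of one index case share a distributor and an informant. If the index case does not deliver the kits, none of that person's contacts can test. If the index case delivers and encourages use, several may test together. Some positive correlation within an index case therefore follows from the way the model works, and 370 contacts carry less information than 370 independent people.

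Contact uptake is the main outcome of this use case, and section 2.7 intends it to inform national policy on contact tracing. If recruitment stopped near 370 and the team took the minimum as met, the estimate would be less precise than the protocol promises.

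**Working it through.** **Inputs from the protocol.** Uptake p = 0.60, half-width d = 0.05, 95% confidence (z = 1.96), minimum n = 370, contacts per index case m = 3 + 2 = 5, expected index cases 600, expected contacts 600 × 5 = 3000.

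**Input assumed.** The ICC, taken from 0.05 to 0.5, with 1 as the limit at which all contacts of an index case behave alike.

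**Step 1: reproduce the stated figure.** n = z²p(1−p)/d² = 1.96² × 0.6 × 0.4 / 0.05² = 368.8, so 369. This is the 369 of section 5.8 and, rounded, the 370 elsewhere. At n = 370 the half-width is 1.96 × √(0.24/370) = 4.99 points, so any positive correlation takes it past 5.

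**Step 2: allow for clustering.** Design effect DE = 1 + (m−1) × ICC. Half-width = 1.96 × √(0.24 × DE/n). Contacts needed for ±5 points = 368.8 × DE. With m = 5, 370 contacts come from 370/5 = 74 index cases.

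| ICC (assumed) | DE | Effective n at 370 | Half-width at 370 (points) | Contacts needed for ±5 | Index cases needed | Half-width at 3000 (points) |
|---|---|---|---|---|---|---|
| 0.05 | 1.2 | 308 | 5.5 | 443 | 89 | 1.9 |
| 0.1 | 1.4 | 264 | 5.9 | 517 | 104 | 2.1 |
| 0.2 | 1.8 | 206 | 6.7 | 664 | 133 | 2.4 |
| 0.3 | 2.2 | 168 | 7.4 | 812 | 163 | 2.6 |
| 0.5 | 3.0 | 123 | 8.6 | 1,107 | 222 | 3.0 |
| 1 | 5.0 | 74 | 11.2 | 1,844 | 369 | 3.9 |

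**Step 3: sensitivity to cluster size.** Only adult contacts are listed, and one is enough for eligibility, so the mean may be below five. At ICC 0.3 the half-width with 370 contacts is 6.3 points for m = 3 and 5.7 for m = 2. Unequal cluster sizes work the other way. With mean 5 and an assumed coefficient of variation of 0.5, DE = 1 + (1.25 × 5 − 1) × ICC, which at ICC 0.3 is 2.575 and gives 8.0 points.

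**Step 4: the other reading of 370.** If 370 counts acceptors, the number offered is 370/0.6 ≈ 617. Then ±5 points holds while DE ≤ 617/368.8 = 1.673, that is, up to an ICC of (1.673 − 1)/4 ≈ 0.17.

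**Step 5: how far recruitment must fall.** With five contacts each, ±5 points needs 89 index cases at ICC 0.05 and 222 at ICC 0.5. Against 600 expected, that is 89/600 = 15% and 222/600 = 37%.

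**The case against.** The strongest reply is that 370 is a floor, not a target. The same text expects about 600 index cases and 3000 contacts, all consenting index cases are enrolled, and Table 1 budgets 6,000 self-tests, which is two for each of 3000 contacts. No rule stops this component at 370, whereas the congregate component does stop at its number. Even the professional tests alone (5,000 + 10,600 = 15,600) would at 2% positivity give 312 index cases and 1,560 contacts, more than the 1,107 needed at ICC 0.5. This stands. A reader might infer that the trial will not deliver ±5 points. On the protocol's own recruitment assumptions it will, at any ICC.

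What the reply does not rescue is the minimum itself. A minimum matters when recruitment disappoints. Section 5.1.4 says the number of contacts is not known in advance, and section 10 names an absence of COVID-19 as the main constraint.

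A second reply is that the sample size text can be read as 370 acceptors, which leaves room up to an ICC of about 0.17. That is a fair literal reading. However, the formula yields the denominator, and Table 1 speaks only of contacts. The ambiguity is itself worth removing.

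A reader might also infer that the reported confidence interval will be too narrow. The protocol does not establish that. It specifies exact binomial intervals for the outpatient and congregate components only. For this one, section 5.1.4 lists percentages and counts in an exploratory analysis, and section 5.10.2 asks only for 95% intervals. The method may be set in a statistical analysis plan that is not shown.

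Finally, the size rests on an assumed ICC, and 0.5 implies something close to all-or-none delivery. That is true. The direction needs only an ICC above zero.

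**Conclusion.** The point holds for the stated minimum. The 370 (369 in section 5.8) gives ±5 points only if contacts of the same index case are uncorrelated, which is hard to defend when one person distributes the kits and reports the results. With five contacts per index case and an assumed ICC of 0.05 to 0.5, the minimum gives about ±5.5 to ±8.6 points, and ±5 points needs about 440 to 1,110 contacts from about 89 to 222 index cases. Smaller clusters reduce the shortfall.

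The practical effect is limited. The arithmetic of the formula is correct, the component is descriptive with no test or threshold tied to ±5 points, and the expected sample would meet the target comfortably. The error would bite only if index cases fell to somewhere below 15% to 37% of the number expected, depending on the ICC, or if 370 were taken as a reason to stop.

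**What to change.** In section 5.1.4, and to match in Table 1, the executive summary and section 5.8:
- State an assumed ICC, with a range, and a mean number of contacts per index case.
- Either restate the precision of 370 contacts under that assumption, or give the minimum in index cases as well as contacts.
- Say whether 370 means contacts offered a kit or contacts accepting one, and use either 369 or 370 throughout.
- State that uptake is estimated as a ratio (contacts testing over contacts listed), with its interval computed with the index case as the cluster, for example by a robust variance or a bootstrap over index cases. This is worth doing at any sample size: at 3000 contacts and ICC 0.1, an interval that ignores clustering would be ±1.75 points instead of ±2.1.

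The planned single record per index case already holds what this analysis needs. The cost is a few sentences and a less favourable stated precision, with no new data collection. A larger sample would not remove error from relying on one informant per index case.

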### **Recruitment process**

Recruitment process for secondary distribution of self-test kits will begin with a positive COVID-19 test (index). The same research assistant who conducted the initial consenting and baseline data collection for the other use cases will screen the index case for eligibility and complete the written informed consent for the index. All consenting index cases will then be enrolled in the study. Index cases who decline to participate in secondary distribution of self-test kits component of the study will not be disadvantaged in any way and can opt out of the study if no other follow-up activities are due.

Following written, informed consent, index clients will be shown the self-test kits and how to use them and asked to list the fully anonymized details of any household or other close contacts aged 18 years or above. The index will maintain their own contact list using a Paper Enrollment Log (CC03) to assist them with their organization, distribution and documentation of any subsequent steps taken after testing and reporting back to us. If indicated at this stage, written informed consent will also be taken for the costing piece.

At 14 days after recruitment, the data from the enrollment log will be reported back by the index during a telephone interview. The study team will enter this data into simple aggregate format that will be entered electronically as a single aggregate record for each index case (number of contacts; numbers aged over 65 years; numbers offered self-testing; numbers accepting Day 1 self-testing etc.) provided with a) two KN95 masks for themselves; b) a pack of surgical masks to offer to their contacts; and c) two self-test kits to give to each named contact for use immediately and on day 5.

The proportion of contacts linked to care will also be measured and reported. All contacts will be provided with a study leaflet (NC06B) via the index client that explains clearly where to seek care if the self-test result is positive. Additionally, the leaflet provides phone numbers for the project staff who will be on hand to direct positive contacts to the nearest clinic that provides COVID-19 care.

Outcomes will be collected by telephone interview with the index case two weeks after enrolment. The data from the phone interview will include if the index delivered the COVID-19 self-test kits to the contacts or not, contact used the test kits as advised and if they disclosed the results to index. No personal identifiers will be collected on the contacts, but we will ask the index to identify any known high-risk factors (age over 65 years, or over 50 years with co-morbidity) that would be a potential indication of eligibility for outpatient treatment of the tested contact. If consent has been taken, the participant cost survey will then be administered over the phone as well.

A person shall be considered a contact if they had any one of the following exposures to a confirmed case as suggested by WHO(33):

- face-to-face contact with a confirmed case within 1 meter and for at least 15 minutes;
- direct physical contact with a confirmed case;
- direct care for a patient with probable or confirmed COVID-19 disease without the use of recommended PPE.

### **Inclusion criteria**

Index case patients shall be eligible for inclusion if they are:

1. Tested positive for COVID-19
2. Have at least one adult close contact
3. Do not feel at risk of physical harm, loss of employment or loss of housing from participating
4. Feeling well enough to comfortably conduct the study activities, as determined by participant reports and assessment by study staff.

### **Exclusion Criteria for index case patients**

Index case patients shall be ineligible for participation if they are

1. Are unable or unwilling to provide informed consent
2. Not traceable or able to be interviewed by telephone
3. Unable to demonstrate back how to self-test correctly

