##### **Outcome:**

Proportion of contacts accepting the offer of COVID-19 self-testing from the index client.

Secondary outcomes include an assessment of risk factors of the contacts including vaccination history, and socio-demographics.

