### **Main analysis**

The main analysis relates to exploratory analysis of acceptability (% eligible who accept the offer of secondary distribution of kits to household or other close contacts) and contact acceptability (% contacts who self-test), safety (self-report of any social harms experience by the index patient), numbers of kits distributed, numbers of contacts accepting kits, number of contacts testing at least once, number of contacts with positive immediate or day 5 results, and number of contacts diagnosed within 5 days of symptom onset including asymptomatic contacts.

Qualitative data analysis will be captured by semi-structured interview during which index patients will also be asked about any perceived benefits and regrets, and their willingness to recommend secondary distribution to others testing positive for COVID-19.

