#### Overall data tools

Data tools for the different components of the project have been developed by the investigators. For the HCW component, potential participants shall be screened for eligibility (Appendix 7 - CH00: Eligibility screening) before recruitment. A structured questionnaire (Appendix 8 - CH01A :Healthcare workers baseline questionnaire) shall be used to collect data on the participants' demographic characteristics, assess their risk for severe COVID-19, knowledge on basic facts about COVID-19 and their practices and behaviours regarding COVID-19 prevention at baseline in both study arms. Another structured questionnaire (Appendix 9- CH02: Healthcare worker follow-up) shall be used to follow-up the participants monthly up to three months to find out if they had any COVID-19 symptoms over the past four weeks. For those who had the symptoms, we will ask about the management and care they received. After the three months follow-up period, a structured questionnaire (Appendix 10 - CH03: Healthcare worker exit) shall be used to conduct an exit interview where we will reassess the participant's risk for severe COVID-19, knowledge on basic facts about COVID-19, absenteeism from work due to COVID-19, their practices and behaviours regarding COVID-19 prevention, COVID-19 related stigma and discrimination, and experiences with COVID-19 self-testing.

For the PSI-led provider-delivered COVID-19 Ag-RDT testing at OPDs and congregate settings, eligibility screening shall be conducted using Appendix 11 (CP00) and Appendix 13 (CW00) respectively. Structured questionnaires (Appendix 12- CP01: OPD Questionnaire and Appendix 14 – CW01) shall be used to collect data on the participants' socio-demographic characteristics, assess for COVID-19 symptoms, willingness to test and follow next steps on COVID-19 prevention if positive.

For the contact tracing study, potential participant shall be screened for eligibility (Appendix 15 - CC00: Eligibility screening) before recruitment. A structured questionnaire (Appendix 16 - CC01:

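### Secondary distribution: contact counts and contact outcomes both come from one telephone call with the index case, so uptake and social harms describe reached index cases only

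*Protocol*

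**What the plan says.** All references are to the Protocol.

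- **Eligibility.** Sections 5.1.4 and 5.3 both exclude index cases who are "Not traceable or able to be interviewed by telephone". Neither gives a time point. Section 5.9 (Overall data tools) places screening with form CC00 ahead of recruitment: "For the contact tracing study, potential participant shall be screened for eligibility". Section 5.1.4 (Recruitment process) puts screening and written consent first and then says "All consenting index cases will then be enrolled in the study".
- **Contact information at enrolment.** The baseline questionnaire CC01, given when the index tests positive, covers "risk and testing, and information about their close contacts". The index lists adult contacts at enrolment and keeps that list on a paper log (CC03). Two kits are supplied for each named contact.
- **Outcome data.** Section 5.1.4 says "Outcomes will be collected by telephone interview with the index case two weeks after enrolment", and the study team does not telephone contacts. What the index reports at 14 days is put into a simple format "that will be entered electronically as a single aggregate record for each index case". The items named for that record include the number of contacts as well as the numbers offered and accepting. Section 6.2 likewise has the telephone interview record how many adult contacts were eligible and how many tested.
- **Outcome and analysis.** The component's outcome is "Proportion of contacts accepting the offer of COVID-19 self-testing from the index client". The main analysis lists "contact acceptability (% contacts who self-test" and social harms reported by the index. Neither place says which count of contacts is the denominator.

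**The concern.** Contact uptake is the result this component exists to produce (specific objective 5). If the denominator and the numerator are both made at the same call, a missed call leaves no visible gap in the proportion, because a whole household or contact group disappears from both sides of the fraction.

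Non-response here is unlikely to be unrelated to outcome. Index cases who did not hand out kits, lost the log, fell ill or met a bad reaction at home are plausible non-responders. The social-harms result shares the gap, since harms are also solicited by telephone.

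Section 2.7 says the component should help show whether national policy could adopt a more nuanced approach to contacts. For that purpose it matters whether the figure describes all contacts for whom kits were handed out, or only those whose index case answered the telephone.

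**Working it through.** **1. The plan's own figures (5.1.4 Sample size)**

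- Index cases: 30,000 tests x 2% = 600. Contacts: 600 x (3 + 2) = 3000.
- Precision at 60% uptake, +/-0.05, 95% confidence: n = 1.96² x 0.60 x 0.40 / 0.05² = 368.8, rounded up to 369. Section 5.8 states 369 and section 5.1.4 states 370, so the figure is reproduced.

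**2. Where each quantity comes from**

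| Quantity | At enrolment | At the follow-up call |
|---|---|---|
| Contact information or list | CC01; list on CC03; two kits per named contact | Number of contacts in the aggregate record (5.1.4); eligible adult contacts (6.2) |
| Offered, accepting, tested, result | None | Only source |
| Social harms reported by the index | None | Only source |

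A baseline count of contacts is therefore obtainable, but the record described in 5.1.4 and 6.2 takes the count from the call.

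**3. Bounds on uptake over all listed contacts**

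Let L be the share of index cases not reached, u the uptake among their contacts, and 0.60 the uptake observed among contacts of reached index cases. With equal numbers of contacts per index case:

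uptake over all listed contacts = (1 - L) x 0.60 + L x u

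The lower bound takes u = 0 and the upper bound takes u = 1. The Protocol gives neither L nor u. The values of L below are assumptions.

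| L (assumed) | Lower, u = 0 | u = 0.30 | u = 0.60 | Upper, u = 1 |
|---|---|---|---|---|
| 5% | 57% | 58.5% | 60% | 62% |
| 10% | 54% | 57% | 60% | 64% |
| 20% | 48% | 54% | 60% | 68% |
| 30% | 42% | 51% | 60% | 72% |

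For example, at L = 20%: 0.80 x 0.60 = 0.48, and 0.48 + 0.20 = 0.68. At L = 30%: 0.70 x 0.60 = 0.42, and 0.42 + 0.30 = 0.72.

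**4. When the possible bias exceeds the planned precision**

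The difference between the reached-only figure and the all-listed figure is L x (0.60 - u). It reaches 0.05 at L = 0.05 / 0.60 = 8.3% if u = 0, and at L = 0.05 / 0.30 = 16.7% if u = 0.30.

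**5. Direction**

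If u = 0.60 there is no bias. If u is higher, the bias reverses: with overall uptake 60%, L = 20% and u = 0.80, the reached-only figure is (0.60 - 0.20 x 0.80) / 0.80 = 55%.

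**6. Sample size does not help**

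At 30% loss, 3000 x 0.70 = 2100 contacts remain, well above 370. Random error stays small. The uncertainty in step 3 comes from selection and does not shrink with numbers.

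**The case against.** The case on the other side has four parts.

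- **The exclusion is a screening rule.** A reader might infer that an enrolled index case who misses the call is reclassified as ineligible. The documents do not support that. CC00 screening comes before recruitment, all consenting index cases are then enrolled, and the criterion sits beside others that are judged at enrolment. This part stands. Later reclassification is only a possible reading of a line without a time point.
- **Contact data exist before the call.** A reader might also infer that nothing is known about contacts until the call. CC01, the enrolment list and the kits issued per named contact contradict that. This stands too, and it makes the repair easy. It does not remove the problem, because 5.1.4 and 6.2 still describe the count as coming from the call and nothing ties the uptake denominator to the earlier list.
- **Handling of missing calls belongs in a statistical analysis plan.** This is partly right: rules for non-response and sensitivity analyses may be in a plan not shown, and their absence is not the point here. The source of the count, however, is fixed in the Protocol. An analysis plan can use a baseline denominator only if the study has recorded one.
- **Counting unreached contacts as not tested is a worst case.** This is correct. The stated outcome concerns contacts accepting an offer, and some contacts of unreached index cases will have been offered kits and used them. The all-listed figure with u = 0 is a lower bound and should not replace the main estimate.

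**Conclusion.** The point holds in this form: followed as written, the data flow removes each unreached index case together with all their contacts, so uptake and social harms are estimated for reached index cases only. The undated exclusion is a secondary matter of wording.

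The size is conditional. With 60% observed among the reached and equal numbers of contacts per index case, uptake over all listed contacts is bounded by 48% and 68% at 20% loss and by 42% and 72% at 30%. In the worst case, 8.3% loss already uses up the +/-5-point margin. The loss rates are assumed, as is uptake among contacts of unreached index cases.

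It would go too far to say that uptake is overstated. That is the plausible direction if non-responders delivered fewer kits, but the documents give no information on it and the bounds extend above 60%.

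**What to change.** 1. **Exclusion criterion (5.1.4 and 5.3).** State that it is applied once, at CC00 screening, in terms knowable then (for example, no telephone number on which the index agrees to be called). Add that an enrolled index case is not excluded for later non-contact.
2. **Denominator (5.1.4 Recruitment process and 6.2).** State that CC01 records the number of contacts listed at enrolment and that this number is the denominator for uptake. Reconcile the passages that take the count from the telephone call with those that collect it at baseline.
3. **Main analysis (5.1.4).** Report uptake among contacts of reached index cases. Beside it, give a lower bound over all listed contacts (contacts of unreached index cases counted as not tested) and an upper bound (all counted as tested). Give the number of index cases not reached and their listed contacts. Report social harms with the number of index cases interviewed as denominator.
4. **Call window.** Give one window for the call, so that not being reached is defined. At present it is 7 to 14 days (5.1.4 Activities and 5.9), day 14 or two weeks (5.1.4 Cost and Recruitment process) and day 8 (section 7).

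The cost is Protocol wording, a check that CC01 captures the count, and a few extra lines of analysis. The lower-bound figure will look less favourable and should be labelled as a bound.
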